### 3.2. Sample Size and Statistical Analysis

The assumed stroke rate in the intervention group is 1%, and in the control group 4%, based on reported outcomes from a propensity-matched retrospective study of both techniques consisting of >1500 patients [3,4] (Murzi et al. [3,4]. Based on our calculations, 424 patients per group must be included (i.e., 848 patients in total) to test the primary endpoint with a power of 80%. Overall, we assumed a slightly lower stroke rate in the control group than previously reported (4% instead of 5%) to ensure enrolment of enough patients to achieve sufficient power to test the primary endpoint if the stroke rate turns out to be lower. 

The efficacy of the primary endpoint will be calculated using the chi-square test. The endpoint will be measured and tested using the stroke rate up to 7 days postoperatively in both groups. All other categorical endpoints will be measured using chi-square tests. Secondary endpoints with continuous variables will be compared using the t-test for comparison of means, Kaplan–Meier for survival (log-rank) and chi-square for categorical endpoints. A combined endpoint may be created, consisting of stroke, delirium, and access-site-related complications at 30 days to further assess overall safety of the cannulation routes and to achieve a higher level of sensitivity in detecting complications by both treatments.

An interim analysis will be performed after inclusion of 50% of the patients (424). If a significantly higher stroke rate is shown in one group which exceeds the expected stroke rate, the trial may be stopped and concluded for safety reasons and obvious superiority of one technique. If the actual stroke rate differs from the assumed stroke rate, sample size calculation may be repeated on the basis of interim analysis, and enrolment will be adjusted accordingly.

A study flow-chart detailing the screening, enrolment, and study process can be seen in Figure 4.

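### The halfway look permits a superiority stop on a significant difference with no interim level or alpha reserved; at an ordinary 5% level, type I error is roughly 6–8% at common stroke rates of 2–4%

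*Protocol article*

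**What the plan says.** All of the relevant text is in section 3.2 of the protocol article (Sample Size and Statistical Analysis).

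- Primary test: "The efficacy of the primary endpoint will be calculated using the chi-square test", applied to the stroke rate up to 7 days.
- Planning rates: "The assumed stroke rate in the intervention group is 1%, and in the control group 4" (per cent).
- Size: "424 patients per group must be included (i.e., 848 patients in total) to test the primary endpoint with a power of 80" (per cent). Neither alpha nor sidedness is stated.
- Timing: one interim analysis at half of the patients, 424 in total, so about 212 per arm.
- Stopping: "If a significantly higher stroke rate is shown in one group which exceeds the expected stroke rate, the trial may be stopped and concluded", and this "for safety reasons and obvious superiority of one technique". The rule therefore serves two purposes, and one of them is an efficacy conclusion.
- Adaptation: if the observed stroke rate departs from the assumption, "sample size calculation may be repeated on the basis of interim analysis, and enrolment will be adjusted accordingly".

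**The concern.** A superiority claim can be made at two points, at 424 and at 848 patients. The trigger at the first is a significant difference with no level attached, and the sample size makes no allowance for it. If both looks use the usual 5%, a positive result does not carry the 5% error rate that a reader would assume.

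An early stop would not be rare. At the planned rates about 212 × 0.04 + 212 × 0.01 ≈ 11 strokes are expected at the look, and the chance of p<0.05 there is about one half. A stop would then rest on few events, and results selected for crossing a lenient threshold tend to overstate the effect. The article's Discussion expects the trial to influence guideline recommendations. Section 8 says that patients are being enrolled, and a boundary has little credibility unless it is fixed before the interim data are seen.

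**Working it through.** **1. The plan's own figure.** Inputs from section 3.2: 4% and 1% (mean 2.5%), power 80%. Assumed: two-sided 5%, no continuity correction.

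n = [1.960·√(2·0.025·0.975) + 0.842·√(0.04·0.96 + 0.01·0.99)]² / 0.03² = (0.4327 + 0.1850)² / 0.0009 = 423.97, so 424 per group.

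This matches exactly. The alternatives do not: 422 with unpooled variance, 489 with continuity correction, 334 one-sided, 398 one-sided with correction. The stated size is that of a fixed design with the full two-sided 5% spent at the end.

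**2. Normal approximation for two looks.** The correlation of the interim and final statistics is √(212/424) = 0.707. P(|Z₁|>1.96 or |Z₂|>1.96) = 8.3%.

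**3. Exact check.** Strokes per arm are binomial with a common rate p. The chi-square with x and y strokes and N patients in equal arms is N(x−y)² / [(x+y)(N−x−y)]. It is tested at N=424 and, if the trial goes on, at N=848. The condition that the rate exceeds the expected rate can be read in two ways:
- the higher arm is above 4% (at least 9 of 212);
- arm-specific: femoral above 4%, or axillary above 1% (at least 3 of 212).

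Two-sided type I error:

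| Common rate | p<0.05 twice, no condition | Higher arm >4% | Arm-specific | Final test only | 0.003 / 0.049 |
|---|---|---|---|---|---|
| 1% | 7.3% | 4.3% | 5.8% | 4.3% | 4.3% |
| 2% | 7.8% | 5.7% | 6.7% | 4.7% | 4.8% |
| 2.5% | 8.1% | 6.9% | 7.5% | 5.0% | 5.0% |
| 3% | 8.3% | 7.7% | 8.0% | 5.0% | 5.0% |
| 4% | 8.2% | 8.1% | 8.1% | 4.8% | 4.9% |

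**4. At the planned 1% versus 4%** (exact):

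| Rule | Stops at 424 | Overall power |
|---|---|---|
| p<0.05 twice, no condition | 52% | 84.8% |
| p<0.05 twice, with the condition (either reading) | 39% | 84.1% |
| 0.003 / 0.049 | 11% | 83.2% |
| Single final test at 0.05 | – | 83.2% |

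The exact single-test power of 83.2% and the 80% of the planning formula describe the same test; the formula is an approximation.

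**5. Other boundaries** (normal approximation): O'Brien-Fleming 0.0052 / 0.0480 needs about 428 per arm for 80% power; Haybittle-Peto 0.001 / 0.0497 needs about 425.

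**The case against.** **The 5% interim level is inferred.** The article gives no interim level, and a stricter one may sit in a fuller document. Keeping the fixed-design 424 does not disprove a boundary, since O'Brien-Fleming or Haybittle-Peto adds only 1 to 4 patients per arm. This stands as a limit on the size: every inflated figure above is conditional on p<0.05 at the look. It does not remove the point. The article states a rule, with significance as its trigger and superiority as its conclusion, beside a size that spends all of alpha at the end. If a boundary exists elsewhere, this sentence must be reconciled with it.

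**A flat 8% against 5% is tempting but too strong.** It drops a condition in the quoted sentence. With that condition, about 8% is reached only at common rates of roughly 3% or more; at 1% there is little or no excess over 5%. The figures also count both directions. With the condition, false axillary superiority is 2.8%, 3.4% and 3.9% at 2%, 2.5% and 3%, against a nominal 2.5%.

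**A continuity-corrected chi-square would largely remove the excess.** The two-look error is then 2.2–5.1% at rates of 1–4% without the condition. The text does not exclude it, but 424 matches the uncorrected test.

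**A reader might infer that the condition wrongly blocks convincing evidence**, because eight femoral strokes against none (3.8%, p=0.0043) would not qualify. That does not support the point: p<0.003 would not stop there either. The case against the condition is only that it does not control the error.

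**The stop is discretionary.** True, since the word used is may, but discretion sets no error rate.

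**Conclusion.** The concern holds in conditional form. As written, section 3.2 allows a superiority conclusion at half of the data on an unspecified significance criterion, with no alpha set aside. If the criterion is an uncorrected two-sided chi-square at 5% and the rule is followed, the overall type I error at common stroke rates of 2–4% lies between 5.7% and 8.3%, depending on the rate and on how the condition is read. At 2.5%, the mean of the two planning rates, it is 6.9–7.5% with the condition and 8.1% without. At 1% with the condition it is 4.3–5.8%.

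The documents do not support an unconditional 8%, nor a statement that no boundary exists anywhere. Any further inflation from re-estimating the sample size on interim data is not counted in these figures.

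**What to change.** Before the 424-patient look, replace the superiority part of the stopping sentence with a pre-specified alpha-spending boundary. One choice is Lan-DeMets O'Brien-Fleming: two-sided p<0.003 at the interim and p<0.049 at the end, which holds the exact error at 4.3–5.0% over common rates of 1–4%. Haybittle-Peto would serve as well. Specifically:

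- State the test, its sidedness and the level at each look.
- Do not let the condition about exceeding the expected rate stand in for error control.
- Keep safety monitoring as its own statement, so that the stated safety ground for stopping is not lost when the superiority rule changes.
- Base any sample size re-estimation on the pooled, blinded stroke rate, or recompute the final boundary if enrolment changes; the 0.049 assumes a look at half of 848.
- If a boundary is already set in a fuller document, cite it and align this wording.

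The cost is one paragraph and essentially no extra patients. At 1% versus 4%, the chance of stopping early falls from 39–52% to 11%. Power falls from 84.1–84.8% under the unadjusted two-look rule to 83.2%, essentially equal to a single final test.

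### Section 3.2 most naturally allows sample size to be recalculated from the by-arm interim stroke rates, and the ordinary final chi-square test then exceeds its 5% error rate

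*Protocol article*

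**What the plan says.** All of this stands in Section 3.2 (Sample Size and Statistical Analysis) of the protocol article.

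- Planning assumptions: a stroke rate of 1% with axillary and 4% with femoral cannulation, and 80% power. "Based on our calculations, 424 patients per group must be included", 848 in total. No overall rate is assumed, and alpha is not stated.
- Final test: "The efficacy of the primary endpoint will be calculated using the chi-square test".
- Interim analysis: at 424 patients, half the total. It is comparative: "If a significantly higher stroke rate is shown in one group which exceeds the expected stroke rate, the trial may be stopped".
- Re-estimation, in the next sentence: "If the actual stroke rate differs from the assumed stroke rate, sample size calculation may be repeated on the basis of interim analysis", after which "enrolment will be adjusted accordingly".

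The trigger is any departure from assumption. The section gives no direction, minimum or maximum, and does not say whether the rate is pooled or by arm.

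**The concern.** The calculation to be repeated has two inputs, the stroke rate in each arm. If both are replaced by their interim values, the new sample size is a function of the observed treatment difference. A difference that looks moderate leads to a modest extension, and one that looks small to a large extension. The interim data are then pooled with the later data in a test that treats the final size as fixed in advance. Such a test does not keep its nominal error rate.

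The second problem is precision. At the interim the arm rates rest on a handful of strokes, so a correctly planned trial could be re-sized substantially by chance.

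At stake are the credibility of a superiority claim near the 5% level and the feasibility of a trial whose target could multiply on one or two events.

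**Working it through.** **1. Reproduce the planned size.** Inputs from Section 3.2: 1%, 4%, 80% power. Assumed: two-sided alpha 5%, pooled variance under the null, no continuity correction.

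n per arm = [1.95996·√(2·0.025·0.975) + 0.84162·√(0.01·0.99 + 0.04·0.96)]² / 0.03²
= (0.4327 + 0.1850)² / 0.0009 = 0.38157 / 0.0009 = 423.97, rounded up to **424**.

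This matches the protocol, which supports the assumed alpha and formula.

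**2. Strokes at the interim.** 424 patients in total is about 212 per arm. Expected strokes: 212 × 0.01 = 2.1 and 212 × 0.04 = 8.5, together 10.6.

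**3. Sensitivity to one stroke.** The same formula with the observed arm rates:

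| Strokes, axillary vs femoral (212 each) | Recalculated n per arm |
|---|---|
| 2 vs 9 | 363 |
| 2 vs 8 | 451 |
| 2 vs 7 | 586 |
| 3 vs 8 | 712 |
| 3 vs 7 | 1,015 |

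**4. Distribution of the recalculated size when 1% vs 4% is exactly true** (1,000,000 simulated interims): median 427 per arm, quartiles 253 and 816, 5th-95th percentile about 156 to 8,220. It exceeds 848 per arm in 23.5% of trials. Values below 424 occurred only where the interim difference was already significant at 5%.

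**5. Type I error.** 1,000,000 simulated trials per setting: equal true rates, 212 per arm at the interim, n recalculated from the two arm rates, then an uncorrected chi-square test at 5%. The article gives no limits, so floors of 213 or 424 and caps of 848 or 2000 per arm are assumed. Ranges run over those limits.

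| Design | Rate 1% | Rate 2.5% | Rate 4% |
|---|---|---|---|
| Fixed 424 per arm, one test | 4.3% | 4.9-5.0% | 4.8% |
| By-arm re-estimation alone, either direction | 5.8-6.5% | 6.8-7.4% | 6.7-7.5% |
| By-arm re-estimation alone, increase only | 5.5-6.3% | 6.1-6.7% | 5.9-6.7% |
| Unadjusted 5% interim stop alone | 7.3% | 8.1% | 8.2% |
| Stop plus by-arm re-estimation | 8.5-9.3% | 9.1-9.8% | 9.2-10.0% |

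The increment over the stop alone is 8.5 − 7.3 = 1.2 to 9.3 − 7.3 = 2.0 points at a 1% rate, 1.0 to 1.7 at 2.5%, and 1.0 to 1.8 at 4%.

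**6. The alternative.** Use only the pooled interim rate p and keep the 1:4 ratio, so the planning rates become 0.4p and 1.6p. With no unadjusted stop, a floor of 212 and a cap of 1696 per arm, type I error is 5.0%, 5.0% and 5.1% at rates of 1%, 2.5% and 4%. Under 1% vs 4% the recalculated n has median 451 and 5th-95th percentile 277-759.

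**The case against.** The strongest objection is that the sentence speaks of one stroke rate and names no arm. Earlier in Section 3.2 the same phrase is used when explaining why 4% rather than 5% was taken for the control group, where it means a base rate. If only the pooled rate or the control rate were updated at a fixed ratio, type I error would stay near 5% (4.9-5.1% for the control-rate version). This stands as a limit: the by-arm reading is the natural one, because the assumed rates exist only by arm and the interim analysis is comparative, but it is an inference.

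Second, this is a condensed article, and a full protocol or analysis plan may set limits and an adjusted test. That is why the absence of a cap is not itself the point. The article does, however, fix the trigger, the basis, the consequence and the final test, and on the natural reading these do not fit together.

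Four stronger readings are tempting and are not supported:

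- **That re-estimation causes the whole 8.5-10%.** Most of that excess comes from the unadjusted interim stop. Re-estimation adds 1-2 points.
- **That the trial would be shrunk, even below the patients already enrolled.** Such values arise only after a significant interim difference, which the preceding stop rule largely covers. That rule is optional and also requires the rate to exceed expectation, so shrinkage is unlikely rather than impossible.
- **That a revised target would reveal the interim effect to unblinded sites.** Nothing in the article says that a result or new target would be announced.
- **That only increases may be allowed.** Error control does not need this with a blinded pooled rate, and with by-arm rates it is not enough.

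**Conclusion.** The concern holds on the natural reading of Section 3.2. By-arm re-estimation followed by an ordinary chi-square test has a type I error of about 5.5-7.5%, or 5.5-6.7% if only increases are allowed. Correcting the interim boundary would not by itself remove this excess. The recalculated size would also be too unstable to plan from. The excess is modest, and its exact size depends on the assumed two-sided 5% alpha, on the assumed floors and caps, and on 212 patients per arm, which simple randomization will only approximate. The upper end of the size distribution reflects interims with nearly equal arms, where a sponsor would not be bound to follow an optional rule. Whether by-arm rates were intended cannot be settled from the article. If a pooled or control-rate update was meant, the needed change is to say so.

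**What to change.** State in Section 3.2, before the interim analysis takes place, that any re-estimation uses the blinded pooled stroke rate, with the planned 1:4 ratio between arms held fixed and a stated maximum sample size. Type I error from this step is then about 5%, and the final chi-square test needs no correction for it; the interim stop needs its own boundary. If by-arm rates are to be used, specify a combination or conditional-error final test instead. Alpha should be stated in either case. An increase-only rule is optional.

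The cost is a few sentences of protocol text. The downside is that about 10.6 pooled strokes still give an imprecise answer (about 277-759 per arm under the planning rates), and a pooled rate cannot correct a wrong assumption about the relative risk.

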## 4. Data Management

In this study, the randomization of patients assigned to different interventions was conducted using an online randomization tool. The use of such a tool ensures a fair and unbiased allocation of participants to the intervention groups. The randomization process involved assigning each participant a unique identifier and then using the online tool to generate a random sequence of assignments. This method helps to minimize selection bias and ensures that each participant has an equal chance of being assigned to any of the intervention groups. The online randomization tool used in this study provides a transparent and efficient way to allocate participants, enhancing the validity and reliability of the research findings. By employing this randomization method, we aim to ensure the integrity and rigor of our study design.

A simple randomization process was performed using the REDCap database in this study. The purpose of the randomization was to assign participants to different treatment groups in a completely unbiased manner. Therefore, we used the simple randomization application. This method ensures that each participant has an equal chance of being assigned to any of the treatment groups, minimizing potential biases and increasing the reliability of the study results. The randomization process was conducted using the REDCap database, which provides a secure and efficient platform for data management in research studies.

The data will be stored on a secure server in the protected environment of the Study Centre Bonn. A full-time data manager is already employed by our department and is familiar with data export to REDCap. Data handling will be conducted in accordance with the GCP guidelines and current European data legislation. A GCP-compliant eCRF with secured access and an implemented audit trial will be used. Central monitoring with plausibility checks, as well as on-site monitoring, will be implemented following a risk-adapted approach to ensure high data quality. After clearance and final analysis of the data, as well as the publication of study results, the data will be made publicly available.

## 5. Plans to Promote Participant Retention and Complete Follow-Up

After hospital discharge post-surgery, follow-up will be telephone-based; therefore, adherence to follow-up is expected to be high. If the access route of cannulation is switched to another route, the mode of follow-up and clinical testing will not differ from the rest of the study population. There will be intention-to-treat analysis and per-protocol analysis at the time of publication to account for changes in the mode of cannulation.

## 6. Feasibility of Recruitment/Trial Sites

The study will be conducted at high-volume heart valve centers specializing in minimally invasive valve surgery. All patients admitted for minimally-invasive valve surgery at the participating centers will be screened and assessed for their eligibility. CT scans are performed as per the standard of care, and consent will be obtained after CT scans show eligibility for both cannulation routes.

## 7. Discussion

There is evidence that, even in patients without atherosclerotic vascular changes, axillary cannulation may be more beneficial with regard to the development of peri-operative strokes during MIS using extracorporeal circulation. So far, these have been retrospective observations. 

Murzi et al. (2013) conducted a study with 1280 patients comparing antegrade and retrograde flow in minimally invasive mitral valve replacement over a period of 9 years. Retrograde perfusion was shown to increase the risk of stroke (5 vs. 1%) and postoperative delirium (14 vs. 5%). However, the results should be interpreted carefully, since in one-third of patients who underwent retrograde cannulation, the aorta was occluded for cardiac arrest via a balloon occlusion and not via a vascular clamp [3]. 

In another study by Murzi et al. (2016), 1632 patients who had undergone minimally invasive mitral valve replacement were retrospectively reviewed. Anterograde and retrograde cannulation were examined with regard to the postoperative outcome. Patients under 70 years of age were not found to have a significantly higher risk of neurological complications with retrograde perfusion. The patients who were over 70 years old all had increased atherosclerotic risk factors and had a higher risk of stroke [4]. Grossi EA et al. (2012) also showed that patients with severe peripheral vascular disease have a higher risk of stroke as a result of retrograde arterial perfusion. With the decreasing usage of retrograde cannulation, the total frequency of postoperative neurological episodes decreased significantly over the course of the study (from 4.7% to 1.2% over 12 years) [8].

To date, there is only a small number of retrospective studies on the topic of femoral (retrograde) vs. axillary (antegrade) cannulation. Especially in patients without significant atherosclerotic vascular changes, it is not clear whether neurological complications can be avoided by axillary cannulation. Conducting a randomized study in patients with significant atherosclerotic burden would be considered unethical, since an increased stroke risk must be assumed. The studies described above indicated an increased risk with retrograde perfusion, but due to their retrospective nature and missing pre-operative CT data, these studies can only have limited significance. Also, only patients with mitral valve replacement were compared. We intend to analyze these outcomes for all minimally-invasive heart valve surgeries performed via mini-thoracotomy. In conclusion, there is a significant gap in the evidence with regard to cannulation strategies in minimally invasive heart valve surgery. Since more than 30,000 heart valve surgeries are performed annually in Germany, with a significant share being minimally invasive (59% in mitral valve surgery is currently minimally-invasive), reducing the risks of peri-operative stroke further seems to be an important contemporary task. The results of this study will influence guideline recommendations on perfusion strategy in MIS and cardiac surgery overall.

## 8. Trial Status

The trial is registered in the German clinical trials system (DRKS-ID: DRKS00030486) and was approved by the local ethics committee on 19 December 2022. The trial is currently enrolling patients.

